### Statistical hypothesis, methods, and analyses

The formal null hypothesis to be tested in this study is that there is no difference in mean change in SBP over a 12-month period among patients from the intervention and control groups. If a significant difference is found among the three groups, we will perform pairwise comparisons, i.e., Group 1 vs Group 2, Group 1 vs Group 3, and Group 2 vs Group 3. As our main goal is to examine whether the most intensive care (Group 3, the PCTM intervention) is more effective in BP control than usual care (Group 1), the alternative hypothesis in this comparison is that Group 3 shows a significant improvement of BP from baseline to 12 months follow-up.

We will conduct the primary statistical analysis on an ITT basis with full endeavor to acquire a complete dataset of every patient. The collected trial data will be coded and entered into MATLAB version 2014a and SPSS version 22 for statistical analysis. Comparative statistics of means or percentage rates of different study arms will be presented with two-sided 95% confidence intervals (CIs), and statistical tests will be reported as a two-sided significance level of 5%. A fully specified Statistical Analysis Plan (SAP) that includes detailed analytics of the trial datasets will be prepared and completed before locking the database.

Baseline data will be analyzed and presented using numerical summaries and graphical illustrations. We will perform *F* tests for continuous variables and Pearson’s chi-square tests for categorical variables to assess the difference of baseline characteristics among the three groups. To analyze the primary outcome, we will use a linear mixed model to identify the effectiveness while adjusting the baseline using the following covariates as appropriate: baseline SBP, age, gender, BMI, education levels, exercise, drinking patterns, tobacco use, and CHCs. Only those covariates found to be statistically significant to the outcomes will be selected as explanatory variables for inclusion in the final model. All statistical tests are performed using *F* tests. We intend to use Fisher’s protected least significant difference (LSD) method to protect against multiple comparisons, followed by pairwise comparisons between study groups only if the overall *F* test is significant. The secondary endpoints of DBP, HbA1C, blood lipid levels, and medication adherence will be determined separately between baseline and the follow-up time points for patients of the three study arms. The analytical approach will be identical to those described in the above section for primary outcome analysis.

Missing data will be assumed to be missing at random; therefore, the linear mixed model has already accounted for this assumption. We will use multiple imputation methods to analyze the missing data.

We will also carry out subgroup analyses of the primary and secondary outcomes stratified by the following characteristics at baseline: BMI (<24, ≥24), hypertension stage (stage1, stage 2, and stage 3), education level (non-college, college, or above), presence of one or more comorbidities, and self-reported medication adherence. No formal interim analysis of the primary and secondary outcomes is planned, but progress reports will be prepared and presented to PCPs and partnering cardiologists every 3 months.

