### Setting

This study will be taking place in the XuHui District in Shanghai, China. The four participating community healthcare centers (CHCs) are classified as tier 1 clinics; each has approximately 30–40 practicing PCPs, and they provide a full range of primary care services to nearly 330,000 residents in total. Cardiologists are mainly recruited from Shanghai Chest Hospital, which is located in the same district and is one of the largest chest specialty hospitals in the nation. Potentially eligible patients are identified and referred by PCPs from CHCs, where all data collection will be conducted including baseline and follow-up tests, except for home-based BP telemonitoring.

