### Randomization process

We use a block randomization design to ensure balance within CHCs and baseline SBP measurements. We set each CHC as a block, and patients are randomized to three groups in each block with a rate of 1:1:1. A study statistician is solely responsible for generating the randomized allocation sequence using computer software (MATLAB version 2014a) and assigning patients to the intervention or control groups. The allocation sequence is concealed in opaque envelopes from all study researchers until the interventions are assigned. Furthermore, an engineer from CareLinker who does not know the grouping information is in charge of training participants of Groups 2 and 3 to use the BP telemonitor and app in order to ensure an equal level of training between the two intervention groups. Due to the nature of the intervention, the study is an open-label trial to all participating patients, physicians, and coordinators at each site.

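### The primary model keeps only covariates that prove statistically significant, so it is not pre-specified and may drop CHC, the randomisation block

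*Protocol article*

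**What the plan says.** The section on statistical hypothesis, methods and analyses of the protocol article describes the primary analysis: "we will use a linear mixed model to identify the effectiveness while adjusting the baseline using the following covariates as appropriate". The candidates are "baseline SBP, age, gender, BMI, education levels, exercise, drinking patterns, tobacco use, and CHCs", nine in all. The next sentence gives the rule for the final model: "Only those covariates found to be statistically significant to the outcomes will be selected as explanatory variables for inclusion in the final model". It names no threshold and no screening procedure, and it protects no covariate. The secondary endpoints are to be analysed in the same way.

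The section on the randomisation process says: "We set each CHC as a block, and patients are randomized to three groups in each block with a rate of 1:1:1". The stated purpose is "We use a block randomization design to ensure balance within CHCs and baseline SBP measurements". There are four CHCs (Setting section). A full SAP is promised before database lock.

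**The concern.** A confirmatory analysis should have a model that can be written down before the outcomes are seen. Under this rule it cannot: the covariate set is known only after each candidate has been tested against the outcome. The rule is also loose. It does not say whether candidates are tested singly or jointly, at what level, or how selection is to work across the multiply imputed data that the same section plans. Two analysts could follow it faithfully and report different primary estimates.

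CHC is a particular problem. Patients are randomised within CHC, so the analysis should carry CHC as a design feature, whatever its p-value. Here it has to pass a significance test that a trial of this size can easily fail when centre differences are modest. Because the rule also governs the secondary endpoints, SBP, DBP, HbA1C, lipids and adherence could each be analysed with a different covariate set.

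**Working it through.** **The plan's own figure.** The sample size section gives a difference of 7 mm Hg, an SD of change of 16.5 mm Hg, 80% power and two-sided 5%.
- n per arm = 2 × (1.960 + 0.842)² × 16.5² / 7² = 87.2, rounded up to 88.
- With 20% dropout: 88 / 0.8 = 110 per arm, and 3 × 110 = 330.

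The plan's figures are reproduced. The calculation is an unadjusted two-sample comparison, so it does not depend on the covariate rule.

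**Number of possible models.** Nine candidates, each in or out, give 2⁹ = 512 covariate sets. If baseline SBP is always kept, 2⁸ = 256 remain. If all nine were unrelated to outcome and tested independently at 5%, the chance of keeping at least one would be 1 − 0.95⁹ = 37%.

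**Is baseline SBP at risk?** Assume equal SBP variance at baseline and 12 months, with correlation ρ. Baseline then explains a share (1 − ρ)/2 of the variance of change. With 264 completers the expected t statistic is roughly √(264 × R²/(1 − R²)).
- ρ = 0.3: R² = 0.35, t ≈ 11.9
- ρ = 0.6: R² = 0.20, t ≈ 8.1
- ρ = 0.8: R² = 0.10, t ≈ 5.4

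In simulation, baseline SBP was kept in 100% of trials at ρ = 0.3 and 0.6, and in at least 99.9% at ρ = 0.8.

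**Is CHC at risk?** The documents do not give the between-CHC variation, so a range is assumed. Set-up: 3 × 88 completers, four CHCs, baseline SBP plus seven weak covariates, an ordinary linear model for SBP change, and each term kept if p < 0.05 in the full model (CHC on 3 df). In 3,000 null trials per scenario:

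| Assumed between-CHC SD (mm Hg) | CHC kept | F-test error, selected model | F-test error, fixed baseline + CHC |
|---|---|---|---|
| 0 | 4.8% | 5.4% | 4.9% |
| 1.5 | 20.5% | 5.4% | 5.0% |
| 3 | 52.5% | 5.2% | 4.6% |

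A separate simulation, with 2,500 null trials per row, varied CHC's share of the outcome variance. An SD of 3 against 16.5 is 9/272.25 = 3.3%; an SD of 1.5 is 0.8%.

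| CHC share | CHC dropped | F-test error, selected | F-test error, fixed | Group 3 vs 1 error, baseline only | Group 3 vs 1 error, baseline + CHC |
|---|---|---|---|---|---|
| 0% | 95% | 5.0% | 4.7% | 4.6% | 4.5% |
| 1% | 77% | 5.4% | 5.1% | 4.9% | 4.9% |
| 3% | 47% | 5.1% | 4.8% | 4.9% | 5.1% |
| 5% | 32% | 6.3% | 5.8% | 5.1% | 5.4% |
| 10% | 14% | 5.8% | 4.1% | 3.5% | 4.3% |
| 20% | 4% | 5.5% | 4.9% | 2.8% | 5.2% |

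Monte Carlo error is about 0.4 points in both tables. The retention figures agree. In the second simulation the rule picked between 196 and 252 different covariate sets per row. At a 20% share, power for 7 mm Hg in Group 3 vs Group 1 was 90% without CHC and 93% with it.

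**Interval and estimate.** With a true effect of 7 mm Hg, coverage of the 95% interval for Group 3 vs Group 1 was 94.0–95.1% with selection and 94.4–95.2% with the fixed model. Bias was at most 0.1 mm Hg in both. The two estimates differed by 0.1–0.5 mm Hg on average, against an interval width of 8–9.6 mm Hg.

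**The case against.** The strongest reply is that the rule does little measurable damage. Randomisation makes the covariates nearly independent of arm, so selecting among them barely moves the treatment estimate, its interval or the error rate. CHC is dropped mainly when centre effects are small and little is lost. When they are large it is dropped in only about 4–14% of trials, and leaving it out makes the test conservative. All of this stands, and it limits the severity.

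It is also fair that the simulations use a simplified model without repeated visits, a selection procedure that the protocol does not specify, and assumed centre variation.

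Three stronger readings are tempting, and none is supported.
- A reader might infer that the selection is made on unblinded data. The trial is open label to patients, physicians and site coordinators, but the article does not say whether the analyst is blinded.
- A reader might infer that adjustment for baseline SBP could be lost. The text permits it, but at any plausible correlation it would almost never happen.
- A reader might infer that the reported intervals and p-values would be materially wrong because they ignore the selection step. The coverage and error rates above do not show this.

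The promised SAP does not remove the point. The protocol does not leave covariate choice open; it states a rule, and an SAP would have to follow it or contradict it.

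**Conclusion.** The concern holds as a weakness in pre-specification. The rule makes the primary model, and each secondary model, depend on the trial's own outcome data, and it lets the randomisation block fall out of the analysis. For between-CHC SDs of 0 to 3 mm Hg, CHC would be kept in about 5% to 53% of trials. This rests on 88 completers per arm, an SD of change of 16.5 mm Hg, selection at 5% from the full model, and assumed centre variation. The effect on type I error (about 5–6%) and on coverage (about 94–95%) is small. It should be corrected because a reader could not confirm that the reported model was the intended one, and because the analysis may not match the design. It is not a case of material alpha inflation.

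**What to change.** Delete the sentence that selects covariates by significance. State that baseline SBP and CHC are in the primary model whatever their p-values, and that each secondary model keeps CHC and the endpoint's own baseline on the same terms. Use the other seven covariates only as a set fixed before outcome data are examined; one pre-named sensitivity model containing all seven is a simple choice, though not the only acceptable one. Carry the same wording into the SAP.

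The cost is a change of wording in the protocol and SAP. Baseline SBP and CHC are already recorded, the number of possible primary covariate sets falls from 512 to one, and the sample size stays at 88 per arm, 110 after dropout and 330 in total.

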#### Secondary outcomes

The key secondary endpoints are changes in mean DBP and hypertension control rate defined as BP <140/90 mm Hg or <130/80 mm Hg (for patients with diabetes or renal diseases) following the national guidelines [21] and changes in measures related to hypertension complications (HbA1C, body mass index (BMI), and lipid levels) from baseline (T1) to 6 months (T2) and 12 months (T3). The other secondary outcome is anti-hypertensive medication adherence, which is assessed by the self-reported, eight-item Morisky Medication Adherence Scale (MMAS) modified to focus on BP drugs at baseline (T1) and 12 months (T3) [20]. These outcomes are measured for the three study groups and compared between the control and intervention groups.

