### Data collection and management

The processes of data collection, storage, analysis, display, and delivery are achieved through the interplay of the web server, web application software, General Packet Radio Service (GPRS)-enabled BP telemonitor, and user-end applications (apps) for patients or physicians. All these components are deployed on computer servers owned by and located within CareLinker and operated behind the company firewall.

Patients’ blood pressures are self-measured using the BP telemonitor (Bliss, Shenzhen China), and the readings are encrypted with the GEA4 algorithm and auto-sent to the web server through the mobile network GPRS protocol. The GEA4 is a widely used encryption algorithm published by the European Telecommunications Standards Institute (ETSI). Each BP telemonitor has its unique device ID bound to one patient ID, the change of which is subject only to the clinical trial administrator in the case of device failure. Auto-submitted BP measures by the BP telemonitor help avoid errors or bias that may otherwise occur in the manual input process. Lab tests of HbA1C and blood lipids are performed at baseline and at each follow-up visit, and the blood samples will not be stored. The test results and other medical information are manually recorded into the patient app by research nurses, and error-checked with format, range, and logic rules built into the app before being sent to the web server. An additional designated research staff will proofread all patients’ health information by comparing with the original reports. The study procedure and data collection are detailed in the SPIRIT figure (Additional file 2).

The user-end apps use Hypertext Transfer Protocol over Secure Socket Layer (HTTPS) to communicate data with the web server. At the sender side, the checksum of the data is calculated by the Message-Digest Algorithm (MD5), encrypted by the Data Encryption Standard (DES) algorithm, and sent out through HTTPS. At the receiver side, the received data are decrypted and their checksum is calculated. Only when the checksum of the received data equals to the received checksum, indicating that the data are not modified during the communication and the integrity is verified, are the received data accepted by the receiver. The HTTPS, MD5, and DES are commonly used communication protocols or encryption algorithms for Internet security. Both apps can be operated on mobile devices running Android 3.0/+ or iOS 7.0/+.

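### The SBP model is carried over unchanged to DBP, HbA1C, lipids and adherence, so no secondary model is assured of adjustment for that outcome's own baseline value

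*Protocol article*

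**What the plan says.** All of the analysis wording is in the protocol article, Statistical hypothesis, methods, and analyses.

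- **Primary model.** For SBP, "we will use a linear mixed model to identify the effectiveness while adjusting the baseline". The candidate covariates, to be applied where appropriate, are given as "baseline SBP, age, gender, BMI, education levels, exercise, drinking patterns, tobacco use, and CHCs". Only covariates that prove statistically significant are kept in the final model.
- **Carry-over.** The outcomes DBP, HbA1C, blood lipids and medication adherence "will be determined separately between baseline and the follow-up time points for patients of the three study arms". The next sentence reads: "The analytical approach will be identical to those described in the above section for primary outcome analysis". Nothing says that each outcome's own baseline takes the place of baseline SBP.
- **Endpoint definitions.** Under Secondary outcomes, "The key secondary endpoints are changes in mean DBP and hypertension control rate". HbA1C, BMI and lipids are also defined there as changes from T1. Adherence (MMAS) is collected at T1 and T3, and the Abstract lists it among the changes.
- **Data available.** Under Data collection and management: "Lab tests of HbA1C and blood lipids are performed at baseline and at each follow-up visit".

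BMI is both a listed covariate and a secondary outcome, but it is not among the four outcomes named in the carry-over. None of those four has its own baseline on the list.

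**The concern.** The list was written for SBP, where baseline SBP is the natural adjustment. Carried over as it stands, the change in HbA1C would be adjusted for baseline SBP but not for baseline HbA1C, and likewise for each lipid and for MMAS.

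A change score and a baseline value of the same measurement are negatively correlated whenever r is below 1 and the variances are similar: patients who start high tend to fall. An arm that starts higher by chance will therefore appear to improve more. Subtracting the baseline over-corrects for the starting difference, and only the baseline as a covariate removes this. The Randomization process section aims at balance on CHC and baseline SBP, not on these four outcomes, so chance differences in them are to be expected.

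At stake are precision, and bias conditional on the imbalance that happens to occur, in the secondary comparisons.

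**Working it through.** **Inputs from the protocol article** (Sample size and power calculation; two-sided 5% level from the statistical section): SBP difference 7 mm Hg, SD of change 16.5; DBP difference 5 mm Hg, SD of change 11.5; 80% power; 88 per group; 20% dropout.

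**Assumed inputs.** The documents give no baseline-to-12-month correlation r and no SBP–DBP correlation q. I take r from 0.3 to 0.8, q from 0.3 to 0.7, and equal variances at both visits.

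**Step 1: reproduce the plan's figure.** n per group = 2[SD(1.960+0.842)/difference]².
- SBP: 2(16.5×2.802/7)² = 87.2, so 88.
- DBP: 2(11.5×2.802/5)² = 83.0, so 84.
- With dropout: 88/0.8 = 110 per group, and 3×110 = 330.

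The stated figures reproduce. They rest on change scores without covariates.

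**Step 2: DBP power on the plain change score.** Standard error = 11.5×√(2/88) = 1.73. Then 5/1.73 = 2.88, and 2.88−1.96 = 0.92, which gives power of 82.2%.

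**Step 3: add own-baseline DBP.** With a common visit SD s, the change-score variance is 2s²(1−r) and the baseline-adjusted variance is s²(1−r²). The ratio is (1+r)/2, so the residual SD is 11.5×√((1+r)/2). One standard error of chance baseline imbalance is s√(2/88) with s = 11.5/√(2(1−r)). The part left in the change-score difference is (1−r) times that.

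| r (assumed) | variance ratio | residual SD | power at 88 per group | 1 SE of baseline imbalance (mm Hg) | part left in (mm Hg) |
|---|---|---|---|---|---|
| 0.3 | 0.65 | 9.27 | 94.7% | 1.47 | 1.03 |
| 0.5 | 0.75 | 9.96 | 91.5% | 1.73 | 0.87 |
| 0.7 | 0.85 | 10.60 | 87.9% | 2.24 | 0.67 |
| 0.8 | 0.90 | 10.91 | 86.0% | 2.74 | 0.55 |

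The gain is about 4 to 12 percentage points of power. In units of the change-score standard error, the part left in is 1.03/1.73 = 0.60 at r = 0.3 and 0.55/1.73 = 0.32 at r = 0.8.

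**Step 4: allow for baseline SBP already in the DBP model.** If baseline SBP predicts DBP change only through baseline DBP, it recovers a share q² of the gain: 9% at q = 0.3, 25% at 0.5 and 49% at 0.7. At r = 0.5, in units where the unadjusted variance is 1, the residual variance is then 0.978, 0.938 and 0.878, against 0.75 with own baseline. Relative to the planned model the ratio is therefore 0.75/0.978 = 0.77, 0.75/0.938 = 0.80 and 0.75/0.878 = 0.85, instead of 0.75.

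**Step 5: HbA1C, lipids and MMAS.** The ratio (1+r)/2 applies under the same assumptions. The documents give no SD, effect size or correlation for these outcomes, so I put no power figure on them.

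**The case against.** The strongest reply is that the sentence is condensed and should not be pressed. It calls the approach identical, not the variables. The approach is a mixed model that adjusts for baseline with covariates as appropriate, and the outcome baseline on the list is that of the outcome being modelled. A statistician would ordinarily put baseline DBP into the DBP model. A fully specified SAP is promised before database lock and could settle the matter. The 0.65 to 0.90 ratio is measured against an unadjusted change score, whereas the plan adjusts for several covariates, and r is assumed.

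Much of this stands. The text is ambiguous and does not expressly exclude own-baseline adjustment, and the ratio is an upper bound on the gain where listed covariates already carry part of the information. But the article is not silent: it names a list and carries the approach over as identical. The charitable reading does not close the gap either, because the significance rule would still decide outcome by outcome whether the own baseline stays in.

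A reader might go further and infer that the collected baseline values are unused. The documents do not support that. These endpoints are mainly defined as changes and are assessed between baseline and follow-up, so each outcome's own baseline is subtracted, or enters as the T1 record of the mixed model. Only the regression-to-the-mean part of an imbalance remains.

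A reader might also infer that false-positive rates are inflated. They are not. Over repeated randomisations chance imbalance averages out and is already part of the change-score standard error.

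**Conclusion.** The point holds as a limited one. As written, no model for DBP, HbA1C, lipids or adherence is assured of its own baseline as a covariate, although the values are collected at T1. Under equal variances and an assumed r of 0.3 to 0.8, own-baseline adjustment would remove 10% to 35% of the variance of an unadjusted change score, somewhat less against the planned model for DBP. DBP power at 88 per group would move from about 82% to between 86% and 95%. Without it, each standard error of chance baseline DBP imbalance leaves about 0.5 to 1.0 mm Hg in the estimated difference.

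This concerns secondary endpoints only. It does not invalidate the comparisons, and the 88, 110 and 330 stand. It is an improvement available from data in hand, not a flaw that threatens the trial's main conclusion.

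**What to change.** Replace the sentence that calls the approach identical with wording such as: *Each continuous secondary outcome will be analysed with the same linear mixed model, with that outcome's own baseline value (DBP, HbA1C, each lipid fraction, MMAS score) as a prespecified covariate in place of baseline SBP. This covariate is always included and is not subject to selection by statistical significance.*

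The cost is one sentence, repeated in the SAP. No new data, visits or patients are needed, and replacing baseline SBP one for one adds no parameter to the candidate model. Because the trial is open-label, the wording should be settled before anyone compares secondary outcomes by arm.
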